# Study protocol of the multicentre, randomised, triple-blind, placebo-controlled MERCURI-2 trial: promoting effective renoprotection in cardiac surgery patients by inhibition of sodium glucose cotransporter (SGLT)-2

**DOI:** 10.1136/bmjopen-2024-095504

**Published:** 2025-05-16

**Keywords:** Cardiac surgery, Randomized Controlled Trial, acute kidney injury

## Abstract

**Introduction:**

Acute kidney injury (AKI) is a major complication after cardiac surgery and is associated with postoperative morbidity and mortality. Currently, no effective therapy exists to reduce the incidence of postoperative AKI. Sodium-glucose cotransporter-2 (SGLT2) inhibitors are effective in reducing AKI in outpatient settings for patients with chronic kidney disease. We hypothesised that perioperative SGLT2 inhibition will also reduce AKI incidence after cardiac surgery according to Kidney Disease: Improving Global Outcomes (KDIGO) criteria.

**Methods and analysis:**

We designed a multicentre, randomised, placebo-controlled, triple-blinded, superiority trial. A total of 784 patients, aged above 18 years, undergoing cardiac surgery will be included with stratification for sex and type 2 diabetes in a 1:1 ratio. Patients will receive either dapagliflozin 10 mg or placebo from the day before until 2 days after surgery. Serum creatinine will be measured preoperatively and daily for the first 7 days after the operation, and urine output will be measured until the urinary catheter is removed. The primary outcome is the incidence of postoperative AKI according to the KDIGO criteria.

**Ethics and dissemination:**

The medical ethics committee of the Amsterdam University Medical Centre (UMC) and the Dutch competent authority approved the study protocol (currently, version 9, 19 January 2024). This is an investigator-initiated study. The Amsterdam UMC, as sponsor, retains ownership of all data and publication rights. After completion of the trial, results will be disseminated to participants, patient societies and physicians via a network meeting and digital newsletter. Results will be submitted for publication in a peer-reviewed international medical journal and presented on (inter)national congresses.

**Trial registration number:**

Clinicaltrials.gov identifier: NCT05590143.

STRENGTHS AND LIMITATIONS OF THIS STUDYA randomised controlled trial using sodium-glucose cotransporter-2 inhibitors to prevent acute kidney injury (AKI) after cardiac surgery.Multicentre, randomised, triple-blind and placebo-controlled.An easily clinically implementable intervention starting only 1 day prior to the operation.Repurposing of a widely-used and safe kidney protective drug.As postoperative AKI is the primary outcome in this study, further research is required to investigate the longer-term impact.

## Introduction

 Annually, more than 2 million cardiac surgeries are performed worldwide, and the incidence of cardiac surgery-associated acute kidney injury (CSA-AKI) is reported to be up to 70%.^1^ Currently, no evidence-based preventive options are available.^2^ The reported incidence varies considerably between countries and centres, which may depend on standards of surgery as well as perioperative care, selected patient population, type of surgery and, perhaps most importantly, disparities in AKI definition and monitoring. The majority (71%) of diagnosed cases of CSA-AKI are classified as stage 1, according to Kidney Disease: Improving Global Outcomes (KDIGO) criteria, which include an increase in serum creatinine of ≥0.3 mg/dL within 48 hours, ≥ 1.5 times baseline within 7 days or urine output <0.5 mL/kg/h for 6–12 hours and resolve without treatment or medical intervention.^3^ However, 12% of cases fall into stage 3, potentially necessitating renal replacement therapy for the management of AKI.^3^ CSA-AKI is independently associated with higher postoperative mortality compared with patients without AKI: 3 times higher mortality for patients with stage 1 AKI and up to 37 times higher for patients requiring dialysis (stage 3 AKI). Patients with AKI also have enhanced length of stay in the intensive care unit (ICU) and hospital and marked increments in cost of care, ranging from 1.21 times higher costs for stage 1 AKI to 2.74 for stage 3 AKI requiring dialysis.^2 4^ In addition, patients with only stage 1 AKI have a higher probability of developing chronic kidney disease (CKD) in the years following surgery, as compared with individuals without postoperative AKI.^5^ The risk of death associated with AKI remains increased for up to 10 years after cardiac surgery, even for those with complete recovery of kidney function.^4 6^ It is evident from these data that CSA-AKI represents a major unmet medical need posing a burden on patients and society.

Despite several attempts with a variety of pharmacological interventions, including vasodilators, diuretics, analgesics, antioxidants, cholesterol-lowering and anti-inflammatory drugs, no successful interventions have been identified that prevent CSA-AKI.^7 8^ However, sodium-glucose cotransporter-2 (SGLT2) inhibitors are promising new drugs to prevent CSA-AKI. SGLT2 inhibitors were initially developed for their glucose-lowering effects by inducing glucosuria.^4^ In addition, they have obtained a prominent place in clinical practice as they reduced progression of kidney disease in patients with CKD with or without type 2 diabetes (T2D) in large outcome trials.^9^ Moreover, in these trials, SGLT2 inhibitors reduced AKI incidence (HR 0.66, 95% CI 0.54 to 0.80), even though it was assessed as a safety endpoint in most trials.^6^ The mechanisms by which SGLT2 inhibitors prevent acute or chronic kidney injury are still the subject of research. SGLT2 inhibitors reduce estimated glomerular filtration rate and glomerular pressure, thereby preventing kidney damage.^10^ Lowering glomerular hyperfiltration reduces kidney oxygen consumption and may thus ameliorate kidney hypoxia, and since oxygen deprivation is a major contributor to CSA-AKI, this might protect against injury.^11^ Furthermore, SGLT2 inhibitors improve haemodynamics and exhibit anti-inflammatory properties.^12 13^ Preclinical data have shown that SGLT2 inhibitors reduced renal ischaemia-reperfusion injury.^14^,^16^ An overview of the proposed advantages of SGLT2 inhibitors in reducing CSA-AKI is shown in figure 1.

**Figure 1 F1:**
[figure not shown]
Overview of the proposed advantages of SGLT2 inhibitors in reducing CSA-AKI. CSA-AKI, cardiac surgery-associated acute kidney injury; EPO, erythropoietin; LV, left ventricle; SGTL2, sodium-glucose cotransporter-2.

We conducted a pilot trial to test the feasibility and kidney protection of SGLT2 inhibitors in the context of cardiac surgery, the Metabolic and Renal outcomes in Cardiac sUrgery patients Receiving SGLT2 Inhibitors (MERCURI), at the Amsterdam University Medical Centre (UMC). This single-centre, open label, randomised, phase IV clinical trial included 55 patients and showed a significant reduction in AKI incidence of 46.7% (95% CI −69.7 to −23.6, p=0.001), comparing the use of an SGLT2 inhibitor (empagliflozin) with the untreated control group.^17^

The current MERCURI-2 trial investigates the effect of perioperative SGLT2 inhibition on the incidence of AKI in patients undergoing cardiac surgery.

## Methods

The MERCURI-2 trial (clinicaltrials.gov identifier: NCT05590143) is a multicentre randomised triple-blind placebo-controlled (1:1) superiority trial in patients undergoing cardiac surgery. The trial is designed to evaluate the effect of dapagliflozin 10 mg once daily, compared with placebo, added to standard of care, on the incidence of CSA-AKI. This is an investigator-initiated study, with Amsterdam UMC as sponsor. The study protocol was approved by the Medical Ethics Committee of the Amsterdam UMC and by the Competent Authorities according to national and international regulations (METC 2022.0795 and EudraCT number 2022-002453-25). The first patient was included in June 2023. The trial has an estimated duration of 3 years.

### Trial population

Our aim is to enrol 784 adult patients (aged above 18 years) scheduled to undergo elective cardiac surgery. Detailed exclusion criteria are listed (table 1). Patients with type 1 diabetes (T1D) are excluded because of the risk of SGLT-2 inhibitor-associated euglycaemic diabetic ketoacidosis (euDKA) in this patient population. For the same reason, patients with a history of DKA are excluded. Furthermore, patients with T2D with body mass index (BMI) <25 kg/m^2^ using multiple daily insulin injections are excluded as they phenotypically resemble T1D, placing them at higher risk for euDKA. Patients with a systolic blood pressure below 100 mm Hg at the time of inclusion are excluded due to the possible blood pressure lowering characteristics of dapagliflozin. Furthermore, patients currently treated with SGLT2 inhibitors or with known or suspected allergy to dapagliflozin are excluded from participation.

**Table 1 T1:** Inclusion and exclusion criteria of the MERCURI-2 trial

Inclusion criteria	Exclusion criteria
Signed informed consent	T1D
Aged above 18 years	T2D with a BMI <25 kg/m^2^ and using multiple daily insulin injections (both short-acting and long-acting insulin)
Scheduled for elective cardiac surgery	History of diabetic ketoacidosis
	Systolic blood pressure <100 mm Hg at time of inclusion
	Reduced kidney function at baseline with eGFR <20 mL/min at time of inclusion
	Current treatment with SGLT2 inhibitors
	Known or suspected allergy to trial products or other drugs in the same class
	Emergency surgery, defined as in need of surgery for medical reasons within 72 hours
	Woman of childbearing potential who is pregnant, breast feeding or intends to become pregnant or is not using adequate contraceptive methods

BMI, body mass index; eGFR, estimated glomerular filtration rate; SGTL2, sodium-glucose cotransporter-2; T1D, type 1 diabetes; T2D, type 2 diabetes.

### Study design

Potentially eligible patients who are scheduled for cardiac surgery will be contacted via telephone, during preoperative hospital admission or during a preoperative hospital visit. Patients will receive both written and oral information (online supplemental file 1). After informed consent is obtained and signed, baseline characteristics such as age, sex, ethnicity, BMI, blood pressure, American Society of Anesthesiologist physical status, medical history and medication use will be collected. The most recent serum creatinine and glycated haemoglobin A1c, if measured as part of standard medical care before surgery, will be recorded. Patients will subsequently be randomised to dapagliflozin or placebo. Patients will take the first dapagliflozin 10 mg or placebo on the day before surgery, between 15.00 and 20.00. The second dosage will be taken on the morning before surgery. The remainder dosages will be taken the first and second day after surgery. In case the surgery is postponed, an additional dose will be administered. Patients with T2D on glucose lowering therapy will be advised on how to adjust their current diabetes treatment to prevent potential hypoglycaemia (figure 2).

**Figure 2 F2:**
[figure not shown]
Treatment algorithm for adjustment of glucose lowering therapy in patients with T2D. DPP4, dipeptidyl peptidase IV; GLP-1 RA, glucagon like peptide-1 receptor agonist; HbA1c, haemoglobin A1c; IU, international unit; SU, sulfonylureas; T2D, type 2 diabetes.

Serum creatinine will be measured daily until day 7 or until discharge from hospital. We aim to collect an additional blood sample from 20% of the participants, both on the day before and after surgery, for potential future analyses. Urine output will be reported as measured during routine medical care, until the urinary catheter is removed. Complications (online supplemental table 1) and ICU and hospital length of stay will be registered until 30 days after surgery. After 30 days, patients will receive a questionnaire measuring patient-reported quality of life and disability with questions from the WHO Disability Assessment Schedule 2.0 (WHO-DAS 2.0), Days at Home in first 30 days (DAH30) and 5-level EuroQol 5-dimensions (EQ5D5L). Data will be collected using Castor EDC (Amsterdam, Netherlands), a good clinical practice compliant data management system.^18^ The study design is summarised in figure 3.

**Figure 3 F3:**
[figure not shown]
Summary of the study flow of the MERCURI-2 trial. AF, atrial fibrillation; DAH30, days at home in first 30 days; ICU, intensive care unit; MACE, major adverse cardiovascular events; MAKE, major adverse kidney events; OR, operation room; QoRquality of recovery; SGLT2, sodium-glucose cotransporter-2.

### Randomisation

After inclusion, patients will be randomised by Castor EDC. Block randomisation with computer-generated blocks of 4, 6 or 8 patients will be used. The block size will be unknown to the researchers. Randomisation is stratified for sex, presence of T2D and study site.

### Allocation concealment and blinding

Investigators will register the patient in Castor EDC. The randomisation outcome will be exclusively visible to the trial pharmacy. Treatment allocation of a patient will only be disclosed in case of a suspected unexpected serious adverse reaction (SUSAR). Study treatment is provided in identical boxes, each containing either six overencapsulated tablets of dapagliflozin or placebo. To ensure blinding, the original 10 mg dapagliflozin (AstraZeneca, Södertälje, Sweden) tablets will be overencapsulated by the good manufacturing practice (GMP) certified trial pharmacy at Amsterdam UMC. The capsules will be filled with microcrystalline cellulose PH102. The matching placebo capsules will solely contain microcrystalline cellulose PH102. Patients, healthcare providers and investigators will be blinded to group allocation until database lock.

### Outcomes and outcome adjudication

The primary outcome of this study is the incidence of AKI according to the KDIGO criteria (table 2) based on serum creatinine and urine output. Serum creatinine levels and urine output will be reviewed by a second investigator and the study monitor to ensure primary outcome adjudication. Other secondary kidney-related outcome parameters include the difference in the primary outcome between men and women, incidence of individual AKI stages according to KDIGO criteria, the maximum change of creatinine postoperatively compared with the baseline creatinine preoperatively, the postoperative creatinine course, the number of patients with persistent kidney failure (defined as creatinine concentration ≥200% of baseline creatinine concentration after 30 days), the number of patients requiring dialysis and the number of patients who died due to a primary kidney-related cause. The cardiac-related secondary outcomes include the incidence of de novo postoperative atrial fibrillation, registered on a 12-lead ECG, the maximum postoperative creatine kinasemyocardial band (CK-MB) or troponin concentrations, the number of patients who developed new onset cardiac arrhythmia, new myocardial infarctions or cerebrovascular accident confirmed by CT scan within the first 30 days postoperatively, as well as the number of patients who required an extended hospital stay due to heart failure, needed readmission for heart failure or died from a primary cardiac cause. Furthermore, length of stay in the ICU and the hospital measured in days and all-cause mortality were collected (table 3). Complications within the first 30 days after surgery (online supplemental table 1) are retrieved from the electronic patient file and collected. The outcomes of the patient-reported quality of life and disability measured with three questionnaires, DAH30,^19^ WHO-DAS 2.0^20^ and EQ5D5L,^21^ will be evaluated across the treatment groups. Safety outcomes of SGLT2 inhibitors such as genital mycotic infections, DKA and hypoglycaemia will be assembled and compared between the treatment groups.

**Table 2 T2:** Definition and staging of acute kidney injury according to kidney disease: improving global outcomes criteria

Stage	Acute kidney injury	Difference	Time frame
1	Serum creatinine	≥0.3 mg/dL (26.5 mcmol/l) or	Within 48 hours
		≥1.5 times baseline	Within 7 days
	Urine output	<0.5 mL/kg/h	For 6–12 hours
2	Serum creatinine	2.0–2.9 times baseline	
	Urine output	<0.5 mL/kg/h	For >12 hours
3	Start renal replacement therapy		
	Serum creatinine	3.0 times baseline or	Within 7 days
		≥4.0 mg/dL	
	Urine output	<0.3 mL/kg/h or	>24 hours
		Anuria	>12 hours

**Table 3 T3:** Recorded secondary and exploratory outcomes

Outcome measures	Time frame	Definition
Secondary outcomes		
Individual AKI stages	≤ 7 days postoperative	Incidence of stage 1, 2 and 3 AKI according to KDIGO criteria
Creatinine	≤ 7 days postoperative	Postoperative maximum change of creatinine compared with baseline creatinine
AF	≤ 7 days postoperative	Postoperative AF recorded with an ECG or for which treatment is initiated
LoS-ICU	≤ 30 days postoperative	LoS-ICU, measured in days from transfer to ICU until discharge from ICU
LoS-Hos	≤ 30 days postoperative	LoS-Hos, measured in days from surgery until discharge from the hospital
MAKE	≤ 30 days postoperative	MAKE. Composite endpoint of death, new dialysis and worsened renal function
MACE	≤ 30 days postoperative	MACE. Composite endpoint of cardiovascular death, nonfatal myocardial infarction, nonfatal ischaemic cerebral vascular accident and hospitalisation for heart failure
Safety outcomes	≤ 30 days postoperative	Genital mycotic infections, diabetic ketoacidosis and hypoglycaemia
Hypoglycaemia	≤ 3 days postoperative	Incidence of hypoglycaemia (blood glucose <4 mmol/L) detected during routine perioperative glucose measurements
Hyperglycaemia	≤ 3 days postoperative	Incidence of hyperglycaemia (blood glucose >10 mmol/L) detected during routine perioperative glucose measurements
Cardiac biomarker 1: troponin	From transfer to ICU until 48 hours postoperatively	Peak troponin concentration as routinely measured during clinical practice
Cardiac biomarker 2: CK-MB	From transfer to ICU until 48 hours postoperatively	Peak CK-MB concentration as routinely measured during clinical practice
Patient-reported quality of recovery 1	Recorded at 30 days postoperatively	According to Days at Home in first 30 days
Patient-reported quality of recovery 2	Recorded at 30 days postoperatively	According to WHO Disability Assessment Schedule 2.0
Patient-reported quality of recovery 3	Recorded at 30 days postoperatively	According to 5 level EuroQol 5-Dimensions questionnaire
Exploratory outcomes		
Systemic haemodynamics 1	From start of anaesthesia until discharge from the ICU, assessed up to 72 hours	Perioperative hourly average heart rate
Systemic haemodynamics 2	From start of anaesthesia until discharge from the ICU, assessed up to 72 hours	Perioperative hourly average mean arterial blood pressure
Systemic haemodynamics 3	From start of anaesthesia until discharge from the ICU, assessed up to 72 hours	Perioperative hourly average cardiac output (L/min)
Urinary oxygenation	From start of anaesthesia until discharge from the ICU, assessed up to 72 hours	Perioperative hourly average mean oxygen tension measured in the bladder
Postoperative LVF	≤ 30 days postoperative	Qualitative assessment (categorised as normal or mildly, moderately or severely reduced function) of LVF as noted by the echocardiographer for routinely performed postoperative echocardiography performed during routine follow-up
Healthcare costs	Recorded at 30 days postoperatively	Using the iMCQ: IMTA (Institute for Medical Technology Assessment) Medical Consumption Questionnaire
Productivity costs	Recorded at 30 days postoperatively	Using the iPCQ: IMTA (Institute for Medical Technology Assessment) Productivity Cost Questionnaire

AF, atrial fibrillation; AKI, acute kidney injury; CK-MB, Creatine kinase myocardial band; ICU, intensive care unit; KDIGO criteria, kidney disease improving global outcomes; LoS-Hos, length of stay in the hospital; LoS-ICU, length of stay in the intensive care unit; LVF, left ventricle function; MACE, major adverse cardiovascular events; MAKE, major adverse kidney events.

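### Urine output alone can define the primary AKI event for a drug that induces glucosuria, and no listed outcome gives creatinine-defined AKI incidence to day 7

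*Protocol article*

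**What the plan says.** The primary outcome, in the section Outcomes and outcome adjudication, is the "incidence of AKI according to the KDIGO criteria (table 2) based on serum creatinine and urine output". In Table 2 a low urine output is sufficient by itself for stage 1, stage 2 or stage 3. The section Primary study outcome compares this pooled incidence between the arms with Fisher's exact test and adds a risk difference with 95% CI.

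On the drug, the Introduction states that "SGLT2 inhibitors were initially developed for their glucose-lowering effects by inducing glucosuria", and also that "SGLT2 inhibitors reduce estimated glomerular filtration rate and glomerular pressure, thereby preventing kidney damage".

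The two components are ascertained differently (Study design): "Serum creatinine will be measured daily until day 7 or until discharge from hospital", whereas "Urine output will be reported as measured during routine medical care, until the urinary catheter is removed".

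Among the secondary outcomes, Table 3 lists "Incidence of stage 1, 2 and 3 AKI according to KDIGO criteria" and, for creatinine, "Postoperative maximum change of creatinine compared with baseline creatinine" up to day 7. The text of the same section adds the postoperative creatinine course, creatinine at or above 200% of baseline after 30 days, and the number of patients who need dialysis. Table 3 also has a 30-day composite of death, new dialysis and worsened renal function.

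**The concern.** Glucose in the urine tends to carry water with it. Dosing runs from the day before surgery to the second day after it, so it overlaps the early postoperative period in which catheter output is recorded. A patient on dapagliflozin might therefore stay above 0.5 mL/kg/h for a reason unrelated to kidney protection and so escape a stage 1 classification that the same patient would receive on placebo. The Introduction puts 71% of cardiac-surgery AKI at stage 1, where this threshold applies.

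At stake is the meaning of a positive primary result. The trial is presented as a test of renoprotection. If the difference came mainly from fewer urine-output-only cases, the primary test alone would not show that. The reader would want the same event counted on creatinine or dialysis, over the same seven days and on the same scale. The article lists no such outcome, and the breakdown by stage inherits the pooled definition.

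**Working it through.** **1. The plan's own figure.** Inputs from Sample size calculation: placebo 22%, intervention 14.1%, 392 per arm, two-sided alpha 0.05, Fisher's exact test. Enumerating both binomial distributions and summing the probability of all tables with Fisher p ≤ 0.05 gives a power of 80.0%. The planned 784 is reproduced. With 22% in both arms, the same enumeration gives a rejection rate of 4.1%. This is the reference for what follows.

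**2. Spurious reduction.** Two inputs are not in the documents and are assumed:
- s, the share of placebo AKI that meets only the urine-output criterion: 30–50%.
- f, the fraction of those cases averted by diuresis alone: 20–40%.

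The creatinine criterion is taken as unaffected in either direction.

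Spurious risk reduction = 0.22 × s × f. Intervention-arm incidence = 0.22 − that value.

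| s | f | Spurious reduction | Share of the planned 7.9 points | Intervention arm | Fisher rejection |
|---|---|---|---|---|---|
| 30% | 20% | 0.22 × 0.3 × 0.2 = 1.32 points | 17% | 20.7% | 6.2% |
| 30% | 40% | 0.22 × 0.3 × 0.4 = 2.64 points | 33% | 19.4% | 13.0% |
| 50% | 20% | 0.22 × 0.5 × 0.2 = 2.20 points | 28% | 19.8% | 10.1% |
| 50% | 40% | 0.22 × 0.5 × 0.4 = 4.40 points | 56% | 17.6% | 30.9% |

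**3. Sensitivity to the assumptions.** At s = 10%, even averting every urine-output-only case gives a rejection rate of only 10%. At s = 36% with all such cases averted, the pooled relative risk is 1 − 0.36 = 0.64, which is the design effect, and rejection is 80%. The result depends almost wholly on two quantities that the article does not state.

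**4. What the listed creatinine outcomes can and cannot show.**
- Maximum creatinine change to day 7 is continuous. It would show no matching benefit if only urine output moved, but it does not count AKI cases.
- The creatinine course is a repeated-measures comparison. It has the same merit and the same limit.
- Creatinine at or above 200% of baseline after 30 days is later and more severe than most AKI events to day 7.
- Dialysis is rarer still: the Introduction puts only 12% of cases in stage 3.
- AKI by stage uses Table 2 with both criteria.

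**5. Power of a creatinine-defined AKI analysis.** Placebo incidence = 0.22 × (1 − s), with a true relative risk of 0.64 and 392 per arm:
- s = 30%: 15.4% versus 9.9%, power 61%.
- s = 50%: 11.0% versus 7.0%, power 45%.

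**The case against.** The strongest reply is that the plan already contains creatinine-only outcomes. Creatinine is followed to day 7 or discharge, while dosing ends on day 2, so the creatinine course extends past treatment. A benefit confined to urine output would find no counterpart there. This stands. A reader might infer that the plan cannot separate the two mechanisms at all, and the documents do not support that. What is missing is narrower: an incidence of creatinine-defined AKI on the same scale and over the same days as the primary outcome.

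Second, the primary outcome matches the stated hypothesis, which is framed in KDIGO terms, and those include urine output. This also stands, and it is why the primary outcome should not change.

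Third, this is a condensed article. A split by criterion may be in the full protocol or the analysis plan, so its absence from the trial is not established. The point rests instead on an outcome definition that the article does fix, beside a detailed outcome list without that split. If the split is already planned elsewhere, confirming it is enough.

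Three further inferences are tempting and go too far:
- The statement that "SGLT2 inhibitors reduce estimated glomerular filtration rate and glomerular pressure" might be read as adding to a false benefit. A lower filtration rate would raise creatinine and so count against the drug. The working sets this effect to zero, so 1.3–4.4 points is not a net figure.
- Catheter removal might be thought to depend on urine flow and so to differ by arm. No section says how removal is decided, and care providers are blinded.
- A renoprotection claim might be made conditional on the creatinine estimate. With 61–45% power, and creatinine itself open to the drug's effect on filtration, that rule is hard to defend.

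**Conclusion.** The point holds in this limited form. The primary event can be met on urine output alone, the drug by the article's own account induces glucosuria, and no listed outcome gives creatinine-defined AKI incidence to day 7. A diuretic effect could therefore contribute to a positive primary result, and the listed creatinine outcomes would only partly show it.

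The size is 1.3–4.4 points, or 17–56% of the planned 7.9, with rejection in 6–31% of trials against 4.1% under the null. It rests on the assumed 30–50% urine-output-only share, the assumed 20–40% averted, no creatinine effect in either direction, and the inference that glucosuria raises urine output. None of these is given in the documents, so the figures show what is possible, not a demonstrated bias. The matter should be addressed, but it does not invalidate the design.

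**What to change.** Keep the primary outcome, its test and the sample size. Before unblinding, prespecify AKI by creatinine or dialysis criteria alone to day 7 as a supportive secondary outcome, reported with a risk difference and 95% CI as for the primary. Show AKI by the urine-output criterion beside it, so that the reader sees which component carries the pooled result. If the full protocol or analysis plan already has this split, name it in the outcome list.

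The cost is one further analysis of data already collected. The downside is limited power: about 61% at a 30% urine-output-only share and 45% at a 50% share, for a relative risk of 0.64. The plan should therefore say that this outcome is read by its estimate and interval, and that a non-significant p-value there does not by itself overturn the primary conclusion.

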### Sample size calculation

Sample size is based on Fisher’s exact test, with an expected AKI incidence in the placebo group of 22%, based on previous cohorts,^2^ taking a conservative estimation. A relative risk of 0.64 based on AKI reduction by SGLT2 inhibitors in previous trials^6^ translates into an absolute risk reduction of 7.9% and incidence in the intervention group of 14.1%. The required total sample size to find such a difference with two-sided alpha of 0.05 and 80% power is 784. We therefore aim to include 392 patients per arm.

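### Persistent kidney failure is defined by creatinine ratio alone, so a patient still on dialysis at day 30 with creatinine below twice baseline counts as a non-event

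*Protocol article*

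**What the plan says.** In the protocol article, Outcomes and outcome adjudication, one secondary kidney outcome is the number of patients with "persistent kidney failure (defined as creatinine concentration ≥200% of baseline creatinine concentration after 30 days". That is the whole rule; nothing elsewhere in the article adds to it.

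Dialysis appears in three other places:

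- The same sentence goes on to list "the number of patients requiring dialysis and the number of patients who died due to a primary kidney-related cause" as further outcomes.
- Table 3 defines 30-day MAKE as a "Composite endpoint of death, new dialysis and worsened renal function".
- Table 2, which stages AKI, has "Start renal replacement therapy" as a stage 3 criterion in its own right, with no creatinine condition attached.

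None of these states whether dialysis is still under way at day 30.

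**The concern.** Once a patient is dialysed, serum creatinine reflects clearance by the machine as well as by the kidneys. A ratio to baseline then no longer measures kidney recovery. Under the stated rule, a patient without recovered function can be scored as free of persistent failure, while a patient with a moderate rise and no need for dialysis is scored as an event.

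The required creatinine also rises with baseline, and the rule has no absolute ceiling. Table 1 excludes only an eGFR below 20 mL/min, so patients with clearly raised baseline creatinine can enrol. They are the ones most easily missed.

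At stake is the meaning of one secondary outcome. It is the only listed kidney outcome meant to separate lasting from transient failure, and it can fail to do so in dialysed patients.

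**Working it through.** **The plan's own figure.** The article gives no expected count for persistent kidney failure. Its one calculated figure is the sample size. The inputs from Sample size calculation are an "expected AKI incidence in the placebo group of 22"%, a relative risk of 0.64, two-sided alpha 0.05, 80% power and 392 per arm.

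- 22% × 0.64 = 14.1%, and 22% − 14.1% = 7.9%, as stated.
- The exact power of Fisher's two-sided test at 392 per arm, 22% against 14.1%, is 80.0%. The total of 784 reproduces, and this point does not touch it.

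**The rule applied to example records.** The creatinine values are invented for illustration.

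| Baseline (mg/dL) | Day 30 (mg/dL) | On dialysis | Ratio | Needed for event (2 × baseline) | Scored |
|---|---|---|---|---|---|
| 1.6 | 2.9 | yes | 2.9/1.6 = 1.81 | 3.2 | no event |
| 2.5 | 4.2 | yes | 4.2/2.5 = 1.68 | 5.0 | no event |
| 1.0 | 2.3 | no | 2.3/1.0 = 2.30 | 2.0 | event |
| 1.0 | 2.9 | yes | 2.9/1.0 = 2.90 | 2.0 | event |

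The first two rows show the failure. The last row shows its limit: at a normal baseline the same on-dialysis value is captured. A value of 2.9 is missed only if baseline exceeds 2.9/2 = 1.45, and a value of 4.2 only if baseline exceeds 4.2/2 = 2.1.

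**Ceiling on the number affected.** The Introduction reports that "12% of cases fall into stage 3, potentially necessitating renal replacement therapy for the management of AKI". Assume that this 12% share applies in both arms, that dialysis starts within the AKI staging window, and that every stage 3 patient is dialysed, is still on dialysis at day 30 and has creatinine below twice baseline.

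- Placebo: 392 × 0.22 × 0.12 = 10.3
- Dapagliflozin: 392 × 0.141 × 0.12 = 6.6
- Total: about 17 of 784

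The floor is 0.

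**A more plausible range.** The article gives no dialysis rate, dependence rate or on-dialysis creatinine. Assume that 25–50% of stage 3 patients are dialysed and 20–40% of those are still dependent at day 30. The multiplier runs from 0.25 × 0.20 = 0.05 to 0.50 × 0.40 = 0.20.

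- Placebo: 10.3 × 0.05 = 0.5 to 10.3 × 0.20 = 2.1 patients
- Dapagliflozin: 6.6 × 0.05 = 0.3 to 6.6 × 0.20 = 1.3 patients
- Difference between arms: about 0.2 to 0.7 patients

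Even these are upper values, because some dialysed patients will still be at or above 200% of baseline and be counted correctly.

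**The case against.** The strongest reply is that the event is recorded elsewhere. Patients who require dialysis are a separate outcome listed directly after persistent failure, and new dialysis is a component of MAKE. A reader might infer that a drug effect on dialysis would be hidden. The article does not support that: the effect would show in two reported outcomes. Keeping a creatinine count, a dialysis count and kidney deaths side by side is also a coherent design, and Table 3 has no row for persistent failure. What remains is that neither dialysis count separates a short course from dialysis still needed at day 30, and the outcome named for persistence does not fill that gap.

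A reader might also set Table 2 against this definition and call it a contradiction. It is not one. Table 2 stages acute injury in the first days; it shows only that the article elsewhere lets dialysis qualify without a creatinine condition.

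A reader might think that the worsened-function component of MAKE needs the same clause. It does not, because a newly dialysed patient is already a MAKE event.

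Finally, the article is a condensed account. The full protocol is available on request and any analysis plan is not shown, so a rule for dialysed patients may exist there. That lowers confidence about how patients will in fact be scored. It does not repair the published definition, which is stated as complete.

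**Conclusion.** The point holds as a minor fault in a stated definition. Read as written, persistent kidney failure excludes a patient who is on dialysis at day 30 with creatinine below twice baseline, mainly where baseline creatinine is raised.

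The number affected cannot be computed from the article. The range is 0 to about 10 placebo and 7 dapagliflozin patients, and on the assumed rates it is probably no more than one or two per arm. The primary outcome, the sample size of 784, the dialysis count and the MAKE total do not change.

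Two larger conclusions might be drawn and are not supported. One is that a large share of true persistent failures is lost: any such share needs an assumed number of captured events and requires every dialysis-dependent patient to fall below the threshold. The other is that the reported rate must be too low in both arms: the number missed may be zero in either arm.

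The point takes a day-30 creatinine as available. The article says "Serum creatinine will be measured daily until day 7 or until discharge from hospital" and does not show where the later value comes from, but that is a separate question.

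**What to change.** Define persistent kidney failure as creatinine at or above 200% of baseline at day 30, or receiving dialysis at day 30 whatever the creatinine. Report how many patients qualify by each route. Leave MAKE as it is.

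Settle the wording before unblinding. Allocation concealment and blinding keeps investigators blinded until database lock, so the clause can be added without knowledge of allocation.

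The cost is one clause and one data item, namely whether dialysis is ongoing at day 30. Complications are already registered to 30 days, so no patients, visits or procedures are added. The outcome will overlap somewhat with the separate dialysis count, which a footnote to the results table can state.
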